## Methods

### Study design

The study is designed as a randomized controlled, single-center, and single-blinded trial, in which participants will be randomly assigned to one of two intervention groups (rumination vs. self-compassion) or a control condition (see “Randomization”) with an allocation ratio of 1:1:1. The study employs a superiority trial design, aiming to determine whether one of the two cognitive coping interventions is more effective in modifying the responsiveness and habituation of biological stress systems compared to the control condition. The design encompasses repeated measurements of each group, i.e., each group will undergo two experimental sessions (t1 and t2) comprising stress test exposures, and within each experimental session, repeated biological and psychological outcome assessments will take place (see Table 1).

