### Power analysis

An a priori power analysis has been conducted using G*Power (version 3.1.9.6) for sample size estimation, based on the findings of a preliminary study [20]. The analysis is limited to the reference biomarkers cortisol and sAA, as no available data provide insights into the modifiability of inflammatory response patterns.

As demonstrated in the aforementioned preliminary study [20], the findings suggest a high modifiability of cortisol and sAA responses through the manipulation of psychological coping mechanisms. Specifically, a large effect was observed in the difference in cortisol response habituation between intervention and control group (*d* = 0.81), while a moderate-to-large effect was found for the difference in sAA response habituation (*d* = 0.67). Based on these findings, medium-to-large effects are expected for differences between experimental groups with regard to their difference in habituation of biological stress system activity. Power analyses revealed a sample size of *N* = 111 (*n* = 37), using an effect size of *f*^2^ = 0.30, *α* = 0.05, 1-*β* = 0.80, number of groups = 3. To address the anticipated 10% dropout rate caused by non-appearance of participants on study day 2 or insufficient biological sample volumes, an additional nine participants (three per condition) will be recruited and tested in this study, resulting in a total sample size of *N* = 120.

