All participants will then be randomly assigned to one of two intervention programs (intervention group 1: rumination, intervention group 2: self-compassion) or to a control condition. Participants will then receive verbal and written instructions for the upcoming task and will be asked to either engage in coping behavior (rumination vs. self-compassion) or to think neutrally about a given topic (e.g., description of everyday life) and to write down their thoughts. To check whether the experimental manipulations were successful, psychological variables will be measured repeatedly before and after each experimental condition via questionnaires (see “Psychological assessments during the experiment”). Upon completion, participants will be dismissed and reminded of the follow-up appointment (+ 1 day) and the incentive they will receive via email. With this email, participants will receive instructions to reflect on the experienced stress situation, to review and complete their notes, and to bring these notes to session 2.

The following day, participants will be scheduled at approximately the same time for experimental session 2. Procedures will closely follow those of experimental session 1, with participants being instructed to review their notes from the previous session and engage in a slightly modified version of the mental arithmetic task during the TSST (i.e., serially subtracting 13 from 2011). In contrast to experimental session 1, no further intervention will take place on this day. At the end of this session, participants will be debriefed and dismissed. To ensure quality control of the experimental procedure, regular audits will take place at intervals of 6 to 8 weeks. These audits will be conducted by a principal investigator who is independent of the data collection process. The audits will include re-training sessions for the TSST panel, as well as for staff members who interact with participants. The objective of these audits is to reinforce adherence to the protocol, address any procedural deviations, and maintain a high standard of data integrity throughout the study.

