### Hypotheses

By increasing either ruminative or self-compassionate thoughts among healthy young adults, the intervention programs are expected to affect the regulation of occurring emotions as expressed by the responsiveness of biological systems during repeated stress exposure.

To check whether the experimental manipulations are successful on a psychological level, self-report measures will be assessed repeatedly over the course of each experimental session and are expected to change over the course of experimental sessions 1 and 2. Specifically, we hypothesize that stress will elicit changes in affect scores and stress appraisals, whereas the two intervention programs are expected to induce changes in affect, self-compassion and rumination, which will be stronger than in the control group (no intervention). Furthermore, we expect these variables to predict indicators of biological stress system activity.

Hypothesis 1: Independent of experimental session and group, stress will elicit significant increases of negative affect and stress appraisals as well as decreases of positive affect.Hypothesis 2: At experimental session 1, stress-induced changes of positive and negative affect and stress appraisals will be indifferent between participants from intervention groups 1 (rumination) and 2 (self-compassion) as well as participants from the control group (no intervention).Hypothesis 3: At experimental session 2, stress-induced decreases of positive affect as well as increases of negative affect and stress appraisals will be strongest in participants from intervention group 1 (rumination) and lowest in participants from intervention group 2 (self-compassion).Hypothesis 4: Increases in state self-compassion and positive affect from pre- to post-intervention will be strongest in intervention group 2 (self-compassion), and increases in state rumination and negative affect will be strongest in intervention group 1 (rumination).

Furthermore, we expect significant responses of biological stress system activity in all experimental groups at each experimental session. Specifically, we expect responses of biological stress system activity to be similar at experimental session 1 and participants from intervention group 2 (self-compassion) to show stronger habituation of stress system activity compared to intervention group 1 (rumination) or the control group (no intervention).

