### Data preparation and statistical analysis

Data preparation and statistical analysis will be performed using IBM SPSS Statistics 26 (IBM Corp., Armonk, NY, USA). Following our pre-registered analysis plan [60], data will be screened for outliers using *z*-scores, and outliers which differ more than 3 standard deviations from the participants’ mean will be excluded from further analysis. In addition, participants will be excluded in case of elevated cortisol levels (e.g., > 12 nmol/L or *z* > 3.29) after arrival at the laboratory (i.e., at baseline) and after accommodating to the testing situation (i.e., at − 1 min relative to the TSST). Additionally, non-adherent participants whose missing values exceed 25% of the data will also be excluded from the analysis. In the next step, Kolmogorov–Smirnov tests will be conducted in order to check for normal distribution. If necessary, data will be log-, ln-, or inverse transformed to reduce skewness of biological data.

To analyze the data (i.e., to compare self-report measures as well as biological response and habituation indices between experimental groups), we will use separate analyses of covariance (ANCOVAs). Sex and BMI will be used as covariates in analyses of biological data, as these two variables have been repeatedly shown to be highly relevant for stress system activity [61, 62]. We will use the standard *p* < 0.05 criteria for determining if the ANCOVA and the post hoc test suggest that the results are significantly different from those expected if the null hypothesis were correct. The post-hoc Bonferroni test adjusts for multiple comparisons.

To investigate associations between primary psychological outcome measures and indices of biological stress measures, we will compute separate hierarchical linear regression models, regressing biological outcome measures onto psychological outcome variables. Again, sex and BMI will be included as covariates in these analyses. When examining state variables, the respective trait variable will be included as covariate in regression analyses.

We expect that certain psychological (e.g., emotion regulation, coping), demographic (e.g., age, gender, sex), and anthropometric (e.g., BMI) variables may be related to biological stress system activity. Therefore, we will test for relationships between these variables and primary outcome measures of biological stress responses in an exploratory fashion.

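### Read as a whole-person rule, the 25% missing-data exclusion drops day-2 no-shows from session-1 analyses for which their data were observed; it should apply per outcome and session

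*Protocol article*

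**What the plan says.** The rule stands in the protocol article under Data preparation and statistical analysis: "non-adherent participants whose missing values exceed 25% of the data will also be excluded from the analysis". It follows one rule that removes outlying values and another that removes participants with elevated cortisol. Its own subject is the participant. The section gives no denominator for the 25% and no definition of non-adherence. It describes its screening as following a pre-registered analysis plan. Outcomes are then compared in separate ANCOVAs.

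The Power analysis section expects an "anticipated 10% dropout rate caused by non-appearance of participants on study day 2 or insufficient biological sample volumes" and adds nine participants to reach 120.

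On the design, "each group will undergo two experimental sessions (t1 and t2) comprising stress test exposures". For day 2, "Procedures will closely follow those of experimental session 1", and "In contrast to experimental session 1, no further intervention will take place on this day". Attendance on day 2 therefore comes after the randomised intervention.

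Under Hypotheses, Hypotheses 2 and 6 concern session 1 only. Hypotheses 1 and 5 cover both sessions. Hypothesis 4 concerns change from before to after the intervention. Affect, stress appraisals and the biological response indices are all listed as primary outcomes.

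**The concern.** Each outcome has its own model, so a participant who lacks an outcome already drops out of that model. For a day-2 no-show, what a whole-person rule adds is the removal of outcomes that were observed.

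Two consequences follow.

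- **Conditioning on a post-randomisation event.** Session-1 responses to the stressor would be compared only among people who returned after the writing task. If returning depends both on the arm and on how strongly a person reacted, the selection can produce arm differences in session 1 that randomisation would not.
- **One data type removing another.** If the 25% is counted over biological values, failed blood sampling can delete a complete cortisol and sAA record. Those are the two markers on which the sample size was based.

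The undefined denominator matters more here than it usually would. The Randomization section says that the analyst knows the group assignments and relies on strict adherence to the pre-registered plan to limit bias. As printed, the rule leaves that analyst a choice.

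**Working it through.** **1. The plan's own figures.** For three groups, power = P(F′ > F₀.₉₅) with 2 and N − 3 degrees of freedom and noncentrality λ = N·f². With f = 0.30 and N = 111, λ = 111 × 0.09 = 9.99 and power is 0.803, so N = 111 reproduces. (The article prints the input as f²; 111 follows from f = 0.30.) Then 111 + 9 = 120.

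**2. Planned biological values per session** (Table 2; Analysis of heart rate variability):

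- cortisol 7 and sAA 7: 14
- five blood markers × 3 draws: 15
- HR, RMSSD and high-frequency HRV × 5 intervals: 15
- total 44 per session, 88 over two sessions

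**3. Planned questionnaire values.**

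- Items per session: PANAS 20 × 5 = 100, BSRI 8 × 2 = 16, SSCS-S 6 × 2 = 12, PASA 16, SSSQ-G 24 × 2 = 48; total 192.
- Screening items: SPS 20, SIAS 20, ADS-L 20, PSS 10, RSQ 32, SCS-D 12; total 114.
- Scale scores per session: 10 + 2 + 2 + 1 + 6 = 21, assuming three SSSQ-G subscales. Screening scale scores: 7.
- Ten demographic fields are assumed where screening is counted.

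**4. Share missing for a day-2 no-show.** With s values per session and c screening values, share = s / (2s + c).

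| What is counted | s | c | Share missing |
|---|---|---|---|
| Biological values only | 44 | 0 | 44/88 = 50% |
| Biological + scale scores | 65 | 0 | 65/130 = 50% |
| The same + screening scores and demographics | 65 | 17 | 65/147 = 44% |
| Biological + items + screening and demographics | 236 | 124 | 236/596 = 40% |
| Saliva + items + screening and demographics | 206 | 124 | 206/536 = 38% |

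For the share to fall to 25%, c would have to reach 2s. At full item level that is 472 screening values, against about 124. So every whole-record count tried is above the threshold. Counted per session, the same person has none of session 1 missing and stays in.

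**5. No usable blood on either day.** Missing values: 15 × 2 = 30.

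- Biological values only: 30/88 = 34.1%, excluded.
- With scale scores: 30/130 = 23.1%, kept.

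The same arithmetic holds for a complete loss of ECG data.

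**6. Loss of precision.** 10% of 120 is 12, leaving 108. The standard error ratio is √(120/108) = 1.054. At f = 0.30, power is 0.836 with 120 and 0.792 with 108. Twelve is a ceiling, because the 10% also covers inadequate samples.

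**7. Selection bias, under assumptions only.** Suppose 4 of 40 in one arm stay away and the tendency to stay away correlates ρ with the outcome. The arm mean shifts by ρ·φ(z)/(1 − p), with p = 0.10 and φ(z) = 0.1755:

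- ρ = 0.2: 0.04 SD
- ρ = 0.5: 0.10 SD
- ρ = 1: 0.1755/0.90 = 0.195 SD

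If all 12 losses fell in one arm, the shifts would be 0.10, 0.25 and 0.50 SD. The document gives no value for ρ or for the split between arms.

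**The case against.** The strongest reply is that the rule is less definite than it looks. The denominator is not given. Non-adherent is not the word that the Power analysis section uses for people who fail to appear; it calls them dropouts. Under Risks, adherence refers to engagement with the intervention and to sample collection. The pre-registered plan is not shown and may settle both points. This stands as a limit on certainty. It does not rescue the sentence, which names participants, the data and the analysis without restriction; if a per-outcome rule is meant, the wording still needs to change.

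A reader might infer that no-shows have complete manipulation-check data which the rule throws away. The document does not establish this. State rumination and state self-compassion are scheduled only 1 min before and 20 min after the stress test. The Abstract places the intervention immediately after the stressor, whereas the procedure describes it after the sampling schedule. If the writing task follows the 20-min reading, a no-show has no later state score. Only affect has a further day-1 reading, at 120 min. The procedure also says that psychological variables are measured before and after each condition, so the point is open rather than refuted.

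A reader might also infer that the rule serves no purpose and should simply be deleted. That goes too far. Under Primary outcomes, the cortisol response is the peak of the readings at 1, 10 or 20 min minus the pre-stress value. With some samples missing, the index can still be computed yet miss the true peak, and the ANCOVA would not notice. A completeness check at the level of the index is worth having.

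Finally, Hypotheses 2 and 6 concern a stressor that precedes the intervention, and using the same cohort as for habituation can be defended for consistency. That is a reason to report such an analysis alongside the full one, not to make it the only one.

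**Conclusion.** The concern holds in limited form. On the natural reading, the rule removes every day-2 no-show (38-50% of planned values missing) and so discards observed data for Hypotheses 2 and 6, for the session-1 parts of 1 and 5, and possibly for affect in 4. At most about 12 of 120 people are involved, and the standard error grows by about 5%. The selection bias could be negligible or material; the range of 0.04-0.20 SD for 4 of 40 lost rests wholly on an assumed correlation and should not be read as an estimate.

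Whether people without blood samples also lose complete cortisol and sAA data depends on the denominator: 34% excludes them and 23% keeps them. It also requires blood to be missing on both days.

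A reader might infer that no-shows are a threat to the main comparison through this rule. They are not. A no-show has no habituation or session-2 value, so the rule changes nothing for that person there.

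The conclusion assumes that the 25% is counted over the whole record and that a no-show counts as non-adherent.

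**What to change.** Replace the whole-person rule under Data preparation and statistical analysis with one applied per outcome and session:

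- Each randomised participant enters every analysis for which the index concerned can be computed from its required samples, and those samples are named for each index.
- Day-1 data of people who do not return stay in the session-1 analyses and, where a post-intervention reading exists, in Hypothesis 4.
- Missing blood or ECG data do not remove cortisol, sAA or self-report outcomes.
- The number missing is reported per outcome and arm.
- The whole-person 25% exclusion, with its denominator defined, is kept only as a sensitivity analysis.

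This takes a few sentences and no new data. The downside is that N differs between outcomes, which a row in the results table can show. If the pre-registered plan already defines the rule this way, the article only needs to say so.

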### Outcome measures

#### Primary outcomes

Primary outcomes will include self-reported measures of affect, appraisals of task-related stress, trait and state rumination, as well as trait and state self-compassion. Further primary outcomes will be response and habituation indices of biological stress measures for HPA axis, autonomic, and inflammatory responses (i.e., cortisol, sAA, HR, HRV, plasma IL-6, cytokine expression rates of IL-6, IL-1β, NF-кB, IкB). To obtain response indices, delta scores will be computed for the initial and repeated exposure to stress using peak values relative to baseline (e.g., peak cortisol values at + 1, + 10, or + 20 min post-TSST minus cortisol values at –1 min pre-TSST). To obtain habituation indices of biological stress measures, values of the second stress response will be subtracted from the first stress response values.

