Hypothesis 5: Independent of experimental session and group, stress elicits significant responses of biological stress system activity.Hypothesis 6: At experimental session 1, responses of biological stress system activity will be indifferent between participants from intervention groups 1 (rumination) and 2 (self-compassion) as well as participants from the control group (no intervention).Hypothesis 7: At experimental session 2, responses of biological stress system activity will be strongest in participants from intervention group 1 (rumination) and lowest in participants from intervention group 2 (self-compassion).Hypothesis 8: Habituation of biological stress system activity will be lowest in participants from intervention group 1 (rumination) and strongest in participants from intervention group 2 (self-compassion).Hypothesis 9: Self-compassion and positive affect will predict lower biological responses to repeated stress, whereas rumination, negative affect, and stress appraisals will predict higher biological responses to repeated stress.Hypothesis 10: Self-compassion and positive affect will predict stronger habituation of biological stress system activity to repeated stress, whereas rumination, negative affect, and stress appraisals will predict lower habituation of biological stress system activity to repeated stress.

We expect these changes to occur among markers of the HPA axis, the autonomic system, as well as the inflammatory system.

Associations of biological stress system activity with other psychological variables (e.g., emotion regulation, coping) as well as demographic (e.g., age, gender, sex) and anthropometric (e.g., BMI) variables will be tested in an exploratory fashion.

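### The session-1 response is collected but not used as a covariate for the session-2 response or the habituation index, which gives up power that could be had for one degree of freedom

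*Protocol article*

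**What the plan says.** All references are to the protocol article.

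- **Primary outcomes.** A response index is the peak minus the pre-stress value, computed in each session. On habituation: "To obtain habituation indices of biological stress measures, values of the second stress response will be subtracted from the first stress response values". Hypothesis 8 therefore concerns R1 − R2 and Hypothesis 7 concerns R2, where R1 and R2 are the session-1 and session-2 responses.
- **Data preparation and statistical analysis.** Response and habituation indices are compared between arms by separate ANCOVAs. "Sex and BMI will be used as covariates in analyses of biological data". The criterion begins: "We will use the standard *p* < 0.05 criteria for determining if the ANCOVA and the post hoc test suggest". Associations are studied by hierarchical linear regression, "regressing biological outcome measures onto psychological outcome variables", again with sex and BMI, plus the trait score when a state score is examined. R1 and arm are not named.
- **Hypotheses.** Hypothesis 6 says of session 1 that "responses of biological stress system activity will be indifferent between participants" from the three groups; Hypothesis 2 says that "stress-induced changes of positive and negative affect and stress appraisals will be indifferent between participants". Neither has a margin.
- **Timing.** The Abstract places assignment directly after the first stress test. Table 2 puts the blood samples at −1, +30 and +90 min; Experimental setting and procedure puts the last one at +120 min and describes assignment only after describing all sampling.

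**The concern.** Where R1 is complete before the intervention, randomisation makes its expected value the same in every arm. The contrasts in R1 − R2, in R2, and in R2 adjusted for R1 then all estimate the same arm effect (apart from sign), and the adjusted one is never less precise apart from the single degree of freedom. The plan uses the other two. A chance imbalance in R1 also stays in the Hypothesis 7 comparison.

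The Power analysis section says that nothing is known about how far inflammatory responses can be modified, so spare precision is worth having.

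Two lesser issues come from the same models. Hypotheses 2 and 6 predict no difference, yet the only stated criterion is a test for difference. And if arm shifts both the psychological predictor and the biological outcome, as Hypotheses 4, 7 and 8 expect, a regression pooled over arms can show the arm effect as individual prediction.

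**Working it through.** **1. The plan's own figure.** Inputs from Power analysis: three groups, α = 0.05, power 0.80, N = 111. One-way noncentral F with noncentrality N·f² and N − 3 error df:

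- f = 0.30 gives N = 111, power 0.803 (also 0.803 with two covariates).
- The article prints "using an effect size of *f*^2^ = 0.30". Taken literally, f = √0.30 = 0.548, which needs only N = 36. The value used was therefore f = 0.30.
- With 10% dropout, 120 × 0.90 = 108, and power for the change score is 0.79.

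That section ties the effect size to differences in habituation, so f = 0.30 is placed on R1 − R2.

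**2. Variances.** Let s1 and s2 be the within-arm SDs of R1 and R2 after sex and BMI, and ρ their correlation.

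- Change score: s1² + s2² − 2ρ·s1·s2
- R2 alone: s2²
- R2 adjusted for R1: s2²(1 − ρ²)

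Change minus adjusted = (s1 − ρ·s2)², and R2 alone minus adjusted = ρ²·s2². Neither can be negative, so the direction does not depend on ρ.

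With s1 = s2 the ratio of adjusted to change-score variance is (1 − ρ²)/[2(1 − ρ)] = (1 + ρ)/2. For one and the same arm effect:

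- adjusted: f = 0.30/√[(1 + ρ)/2]
- R2 alone: f = 0.30·√[2(1 − ρ)]

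**3. Power at N = 108** (ρ is assumed; sex and BMI in every model, R1 added in the adjusted one)

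| ρ | variance ratio | f adjusted | change score | adjusted | R2 alone |
|---|---|---|---|---|---|
| 0.3 | 0.65 | 0.372 | 0.79 | 0.94 | 0.91 |
| 0.5 | 0.75 | 0.346 | 0.79 | 0.90 | 0.79 |
| 0.7 | 0.85 | 0.325 | 0.79 | 0.86 | 0.56 |

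Simulation with 37 per arm (4,000 runs per value of ρ) agrees: change score against adjusted gives 0.81 against 0.94, 0.79 against 0.90, and 0.78 against 0.85.

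Unequal SDs alter the size of the gain. At s2/s1 = 0.8 and ρ = 0.5 the ratio is 0.57; at s2/s1 = 1.2 and ρ = 0.7 it is 0.97, so there is almost no gain over the change score.

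**4. Hypotheses 2 and 6.** With 37 per arm and 108 error df, the 95% half-width of a pairwise difference is 1.982 × √(2/37) = 0.46 SD. If one arm did differ by 0.4 SD, the omnibus test would be non-significant in 60% of trials.

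**5. Hypotheses 9 and 10.** Suppose there is no association within arms, unit within-arm SDs, and arm shifts of ±a in the predictor and ±b in the outcome around a middle arm. The pooled correlation is (2/3)ab/√[(1 + 2a²/3)(1 + 2b²/3)]. Simulation of this simple correlation at N = 108, with a and b assumed:

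| a | b | pooled r | significant at 0.05 |
|---|---|---|---|
| 1.0 | 0.60 | 0.28 | 86% |
| 1.0 | 0.37 | 0.18 | just under half |
| 0.5 | 0.37 | 0.11 | 20% |

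b = 0.37 corresponds to f = 0.37 × √(2/3) = 0.30; b = 0.60 corresponds to f = 0.49.

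**The case against.** The best defence is that nothing here is wrong. Habituation is the construct under study, the index is defined to match it, the change-score contrast is unbiased under randomisation, and the trial was sized on that contrast. This stands. A reader might infer from the table that the trial is underpowered or the comparison biased; the article supports neither, and the size of the gain rests on a correlation it does not give.

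A second objection limits the remedy. If the writing task starts straight after the first stress test, the +30 min and later blood samples follow it. Five of the nine biological outcomes (plasma IL-6 and four expression markers) would then have no post-stress sample before the task, and their session-1 response would be a post-intervention variable. Cortisol peaks at +10 or +20 min could be affected too. This also stands: the adjustment cannot be recommended for every marker as the text now reads.

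Third, the article does not say that p > 0.05 will be read as equality. A reader might infer it, because no other criterion is offered for Hypotheses 2 and 6, but it is not written, and no later step depends on the result. For measures completed before the task, any arm difference is chance.

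Fourth, the regressions are called hierarchical and their steps are not listed, so arm may enter. Variation produced by the manipulation is also part of what the Hypotheses section has in mind. The 86% figure needs an outcome shift well above the planned effect.

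Finally, a reader might conclude that sex, the stratification factor, is left out of the self-report ANCOVAs. The article lists no covariates for them, so that would be inferred from silence. The pre-registered analysis plan, which is not shown, may settle this and other details.

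**Conclusion.** The point holds as a matter of efficiency. The published covariate list for biological data leaves out the session-1 response, and adding it where it is valid would raise power at N = 108 from 0.79 to between 0.94 and 0.86. This assumes f = 0.30 on the change score, equal SDs and ρ between 0.3 and 0.7. Against the session-2 response alone, the gain is small at ρ = 0.3 (0.91 to 0.94) and large at ρ = 0.7 (0.56 to 0.86). The direction is certain for a pre-intervention covariate; the size is not.

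For the inflammatory markers it is open whether a valid session-1 response exists, because the sections on assignment and sampling do not agree.

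The points on Hypotheses 2 and 6 and on Hypotheses 9 and 10 are secondary. The first is a caution on interpretation. The second is a real ambiguity, with a false-association rate from about 20% to 86% depending on assumed arm shifts.

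**What to change.** 1. For each marker whose session-1 response is complete before the writing task, add that response to sex and BMI in the ANCOVAs of the session-2 response and of the habituation index. Both models then give the same arm effect apart from sign, so Hypotheses 7 and 8 rest on one test per marker. Cost: one degree of freedom and a change of wording.
2. Reconcile the Abstract, Table 2, and Experimental setting and procedure on the order of assignment, task and blood sampling. If the +30 min and later samples follow the task, adjust plasma IL-6 and the expression markers only for the pre-stress (−1 min) session-1 value, where the index allows it. Expression data are normalised to each session's baseline, so the value before that normalisation would be needed. Check late cortisol peaks in the same way.
3. Report the session-1 differences of Hypotheses 2 and 6 with 95% confidence intervals, and do not count a non-significant test as support.
4. Add arm to the regressions for Hypotheses 9 and 10. They then use within-arm variation and lose some power.

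The article says that analysis waits until data collection is complete and that the analyst knows the allocation. The change should therefore be dated and recorded in the pre-registered plan before any outcome data are analysed. If that plan already contains these terms, the article's covariate list should be brought into line.
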